### 10.2 Secondary study parameter(s)

Treatment toxicity is assessed with the Common Toxicity Criteria Adverse Events (CTCAE) v5.0 for a period of 24 months from the end of treatment. Toxicity scored as CDLT by the treating physician will be assessed, clarified if necessary, and reconfirmed separately. A severe toxic event is defined as a toxicity assessed as grade 3–5. Toxicities are classified as acute if they first appeared during or up to 3 months after treatment, and are classified as late if they persist, or first appear, more than 3 months after treatment. Multiple occurrences of events of a single toxicity type within an analysis time period are counted as a single event. Median numbers of toxicity events per patient (short-term [acute] toxicity and adverse long-term [late] effects, based on the TAME method of reporting toxicities) are compared between trial arms using t-tests. Proportions of patients affected by one or more toxicity event are compared between trial arms using Fishers exact test. Total administered cisplatin dose will also be recorded and means (or medians depending on the distribution) compared between trial arms.

Overall survival, disease-specific survival, loco-regional recurrences and time to recurrence are measured from the starting date of chemotherapy and compared between the three groups by the log-rank test with all-cause mortality in the intention-to treat population. Deaths are classified as being due to head and neck cancer or to other causes. Recurrences can be loco-regional or distant, or both. Patients who died from head and neck cancer causes as the first event are classed as recurrences. Patients on follow-up and patients lost to follow-up are censored at the last date at which they were known to be alive. Total time of follow-up per patient is two years. Hazard ratios and 95% CIs are generated with a univariate Cox proportional hazards model. The Schoenfeld residuals are tested by plotting the observed Kaplan- Meier values against the Cox predicted values. The effect of randomised treatment on outcome is also assessed after adjusting for known prognostic factors with a multivariate Cox proportional hazards model. At 3 months after treatment semi-structured interviews are conducted to obtain a better understanding of the patients' experience and preference for the treatment schemes, until saturation is reached. Semi-

structured interviews will be analyzed by two investigators using thematic descriptive analyses.

Data coding will be done by open, axial and selective coding and will be supported by the software package NVivo.

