**6.8 Drug accountability**

Together with the local pharmacy, drug accountability according to the GCP guidance will be performed. The pharmacy will not label the IMP as explained in 6.7. Preparation for administration of cisplatin will be performed according to local standard pharmacy procedures. For each administration, patient-named drug accountability, as always done for chemotherapeutic agents, will be done, also according to local standard pharmacy procedures.

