## 8. METHODS

### 8.1 Study parameters/endpoints

#### 8.1.1 Main study parameter/endpoint

The primary outcome parameter is compliance (non CDLT) rate to the proposed cisplatin scheme. Compliance to chemotherapy is defined as the absence of CDLT. CDLT is defined as any toxicity resulting in a cisplatin dose-reduction of  $\geq 50\%$ , a postponement of treatment of  $\geq 4$  days or a definite termination of cisplatin after the first or second cycle of therapy. For weekly cisplatin regimens CDLT is defined as skipped cisplatin treatments or a definite termination of cisplatin before all scheduled cycles of therapy are given.

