## 8.2 Randomisation, blinding and treatment allocation

When the patient has signed informed consent, patients with low SMM will be randomised by the investigator for three-weekly high dose (three cycles 100mg/m^2) or weekly low dose cisplatin (seven cycles 40mg/m^2). Allocation is performed by a central office on-site computer combined with allocations kept in a locked, unreadable computer file that investigators can assess only after the characteristics of an enrolled patient are entered. A stratified permuted-block procedure will randomise patients to the groups on a 1:1 ratio. Strata comprises center and two groups according to AJCC staging:

- 1) Stage I-III
- 2) Stage IV.

Neither patients, investigators nor office personnel are blinded to the group chosen by the allocation procedure.

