## 8.3 Study procedures

All patients diagnosed with an indication for primary CRT, will be identified and screened for eligibility at a weekly multidisciplinary head and neck oncology meeting. SMM will be measured on routinely performed pre-treatment (PET-)CT or MRI of the head and neck. During the multidisciplinary meeting, it will be decided whether the patient has an indication for primary CRT. If the patient is considered for cisplatin CRT, the investigator will inform the patient about the study and asked to sign informed consent. Patients with normal or high SMM (>43.2 cm^2/m^2) will receive the standard cisplatin scheme, which differs per centre. This will either be three-weekly high-dose cisplatin of 100 mg/m^2 or a weekly low-dose cisplatin of 40 mg/m^2. Patients with a low SMM ≤43.2 cm^2/m^2 will be randomised for either low- or high-dose cisplatin, respectively 40 mg/m^2 or 100 mg/m^2. Dependent on each centre, the local pharmacy or the local pharmacy and study pharmacy will be involved since treatment with cisplatin is standard of care and the planned cumulative dosage for both groups will be comparable.

The 100 and 40 mg/m^2 schemes differ in dose and frequency, but also in administration: three times hospital admission versus 7 day visits at the (outpatient) clinic. Because every patient receives radiotherapy daily (which is part of the standard of care), no additional hospital visits are required. In case of CDLT, the treating physician will decide which therapy is most suitable to the patient. It is conform standard guidelines to switch to different type of therapy when cisplatin has become too toxic. There will be no cross-over from the high to low-dose group, since this is against standard of care in which cisplatin therapy is stopped and carboplatin is given instead. The data will still be eligible for analysis in this research. During treatment, the patient will frequently be seen by the treating radiotherapist and oncologist. Adverse events, such as toxicities and CDLT are reported in the EPR according to standard hospital guidelines. Two to three days after each cisplatin dose, the kidney function will be determined. The investigator will collect clinical relevant data for each week of treatment. Data collected include CDLT, cause and type of acute toxicity, grade of toxicity according to Common

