### 10.1 Primary study parameter(s)

The primary outcome parameter is compliance (non CDLT) rate to the proposed cisplatin scheme in the intention-to-treat population.

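### The only stated check on the primary endpoint starts from events the treating physician has already scored as CDLT, so it can confirm or remove events but cannot add one

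*Protocol*

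**What the plan says.** Section 10.1 fixes the endpoint: "The primary outcome parameter is compliance (non CDLT) rate to the proposed cisplatin scheme in the intention-to-treat population". Section 8.1.1 defines the event. The general definition begins "CDLT is defined as any toxicity resulting in a cisplatin dose-reduction of" at least 50%, and adds a postponement of at least 4 days or definite termination after cycle one or two. A separate sentence covers the other schedule: "For weekly cisplatin regimens CDLT is defined as skipped cisplatin treatments or a definite termination of cisplatin before all scheduled cycles of therapy are given".

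The verification step is in section 10.2, under the secondary parameters: "Toxicity scored as CDLT by the treating physician will be assessed, clarified if necessary, and reconfirmed separately".

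Section 8.2 describes an open trial: "Neither patients, investigators nor office personnel are blinded to the group chosen by the allocation procedure". The treating physician is not named there, but whoever prescribes a weekly or three-weekly scheme knows which one it is.

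Other records are planned. Section 8.3 has "Adverse events, such as toxicities and CDLT are reported in the EPR according to standard hospital guidelines" and also "The investigator will collect clinical relevant data for each week of treatment". The weekly items include CDLT, the cause and grade of toxicity, and changes of treatment strategy. Section 10.2 records total cisplatin dose as a secondary outcome. Section 6.8 adds "For each administration, patient-named drug accountability, as always done for chemotherapeutic agents, will be done". None of these is linked to the confirmation of CDLT.

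**The concern.** The recheck is entered only through a positive score from a physician who knows the arm. If that physician attributes a dose change to something other than toxicity, or does not label it, the stated recheck does not reach the patient. A confirmation step limited to positives can correct false positives but not false negatives.

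There is reason not to take equal under-scoring for granted. The general definition requires that toxicity caused the change, while the weekly sentence does not repeat that condition, so the room for judgement differs by schedule. The setting differs too: three admissions against seven day visits (section 8.3). Recording follows hospital routine in five centres. With 33 patients per arm in the calculation, a few misclassified patients can move the primary result.

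**Working it through.** **Step 1: direction of the check.** Let S be the number of patients scored as CDLT and R the number of these that are not reconfirmed, with R ≥ 0. The confirmed count is S − R ≤ S. Confirmed compliance is therefore at least the physician-scored compliance in every group. This follows from the sentence in 10.2 and needs no assumption.

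**Step 2: the plan's own figure.** Inputs from section 4.4: compliance 55.7% (three-weekly) and 86.3% (weekly), two-sided alpha 0.05, power 80%, 33 per arm, 5% drop-out, 70 in total.

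- Pooled normal formula: n = [1.960·√(2·0.710·0.290) + 0.842·√(0.557·0.443 + 0.863·0.137)]² / 0.306² = (1.258 + 0.508)² / 0.0936 ≈ 33.3, so 34 per arm against 33 stated. The figure is reproduced to within one patient.
- At 33 per arm, power is 79.6% by this formula and 81.4% by exact enumeration of the uncorrected chi-square test. 66/0.95 gives 70.

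**Step 3: misses in the weekly arm only, no true effect.** Assumption: true CDLT is 44.3% in both arms and a share m of weekly CDLTs goes unscored. Apparent weekly compliance is 1 − 0.443·(1 − m). The rejection rates are exact, at 33 per arm. Both tests are shown because section 10 lists both without assigning one to the primary outcome.

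| m (assumed) | Weekly compliance | False difference | Share of planned 30.6 points | Rejection, chi-square | Rejection, Fisher |
|---|---|---|---|---|---|
| 0% | 55.7% | 0 | 0 | 6.2% | 3.4% |
| 10% | 60.1% | 4.4 points | 14% | 7.8% | 4.5% |
| 20% | 64.6% | 8.9 points | 29% | 12.9% | 8.1% |
| 30% | 69.0% | 13.3 points | 43% | 21.7% | 14.7% |

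In patients, 33 × 0.443 = 14.6 CDLTs are expected in the arm, so these miss rates mean about 1.5, 2.9 and 4.4 patients.

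**Step 4: misses under the planned rates.** Power = Φ{[d·√33 − 1.960·√(2·p̄·(1 − p̄))] / √(p₁(1 − p₁) + p₂(1 − p₂))}, where d is the apparent difference and p̄ the mean of the two apparent compliance rates.

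| Misses (assumed) | Three-weekly | Weekly | Difference | Power |
|---|---|---|---|---|
| None | 55.7% | 86.3% | 30.6 points | 79.6% |
| 10%, three-weekly only | 60.1% | 86.3% | 26.2 points | 68% |
| 20%, three-weekly only | 64.6% | 86.3% | 21.7 points | 54% |
| 10%, both arms | 60.1% | 87.7% | 27.5 points | 73% |
| 20%, both arms | 64.6% | 89.0% | 24.5 points | 66% |

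The same gap can thus create a difference or hide one, depending on where the misses fall.

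**The case against.** The sentence in 10.2 does not say that the physician's score is the only source of the endpoint. Section 8.1.1 defines CDLT by events, most of them objective, and does not mention physician scoring. The investigator's weekly collection covers unscored patients too, and total dose is recorded. A reader might infer that unscored patients are taken as compliant without review, or that a missed event can never be found. The documents do not support either statement: the data that could expose a missed event are collected. This objection stands. What remains is that no stated step compares those data with the CDLT status, and the one confirmation step that is stated runs in one direction.

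A reader might also infer a bias in favour of the weekly schedule, since section 11.4 expects fewer and milder side effects there. That is a hypothesis, and section 13.2 says there is no evidence and that the opposite may hold. The toxicity condition, where judgement enters, is explicit in the general definition and not repeated in the weekly one. Misses are therefore at least as plausible in the three-weekly arm, where they would work against the weekly schedule.

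Removing a wrongly labelled event is a correction and not in itself a bias. Finally, derivation detail may sit in an analysis, data management or monitoring plan that is not shown. That would excuse silence, but here the protocol itself states the scope of the check.

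**Conclusion.** The point holds as a statement about the check written in section 10.2: it can confirm or remove primary-endpoint events but cannot add one, and the records that could are not tied to it. It is worth changing in an open-label trial of this size.

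The size and direction of any bias cannot be derived from the protocol, because it gives no miss rate. The 10% to 30% range is assumed. Within it, misses confined to the weekly arm with no true effect give a false difference of 4.4 to 13.3 points. Misses of 10% to 20% confined to the three-weekly arm under the planned rates bring power down to about 68% and 54%. These figures show sensitivity and do not predict what will happen. Because most elements of CDLT can be read from dosing records, actual misses may be few, and for the same reason a complete derivation is feasible.

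**What to change.** Replace the sentence in 10.2 and place the new one under 10.1, where the primary endpoint is handled:

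> *CDLT status is derived for every included patient (both randomised arms and the normal-SMM group) by applying the section 8.1.1 definition to the dose and date of each cisplatin administration; every deviation meeting that definition is reviewed for its cause in the same way, whether or not the treating physician scored it as CDLT.*

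The rule must cover all three groups. Section 3 compares compliance across them, and a rule for the randomised patients alone would leave the normal-SMM group ascertained differently.

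Cost: the existing team reviews the charts of all included patients, about 129, instead of only those scored as CDLT. Dose and date per administration must be entered in the trial database; section 6.8 promises accountability under local pharmacy procedures but does not say that these items reach the database. Sample size, treatment and patient burden do not change.

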## 10. STATISTICAL ANALYSIS

Categorical data will be represented as a number and percentage of the total. Data analysis will be performed using statistical software R and SPSS Statistics. A test for normality (Kolmogorov-Smirnoff test) and histograms will be used to assess whether continuous variables are normally distributed. Continuous data will be represented as mean  $\pm$  standard deviation (SD) if normally distributed, and median  $\pm$  interquartile range (IQR) if skewed. Fisher's exact tests, Pearson Chi square tests, independent sample t-tests and Mann-Whitney U tests will be used to assess group differences. All analyses will be two-sided and  $p < 0.05$  is considered significant. Missing data will be handled using multiple imputation, if needed; we only expect few missing data to occur due to the nature and scale of the study.

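### Section 10.2 reports median toxicity counts per patient but tests them with t-tests, so the p value refers to means and not to the reported quantity

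*Protocol*

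**What the plan says.** Section 10.2 defines the variable and its analysis. Repeats of one toxicity type are collapsed: "Multiple occurrences of events of a single toxicity type within an analysis time period are counted as a single event". Each patient therefore has a small whole number for the acute period and another for the late period. The summary is "Median numbers of toxicity events per patient (short-term [acute] toxicity and adverse long-term [late] effects", and the same sentence ends "based on the TAME method of reporting toxicities) are compared between trial arms using t-tests". No other test is named for these counts, and the sentence has no clause that lets the distribution decide. The next comparison of a per-patient quantity in that section, cumulative cisplatin dose, does have one: "means (or medians depending on the distribution) compared between trial arms".

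The opening of section 10 gives a general rule for continuous data, with the mean and SD used "if normally distributed, and median $\pm$ interquartile range (IQR) if skewed". It also lists the tools: "independent sample t-tests and Mann-Whitney U tests will be used to assess group differences". That list assigns no test to any endpoint.

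**The concern.** The protocol fixes a median as the reported quantity and a test of means as its p value. By its own general rule, choosing the median signals that skewed data are expected. The median of a small integer count moves in whole or half steps. Two arms can therefore share a median while their means differ, or have different medians with almost the same mean. In either case the p value does not describe the two numbers beside it.

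Toxicity is a listed secondary objective, and the rationale for the weekly scheme is better tolerance. Readers will set the toxicity table beside the compliance result, so the p value in that table should belong to the quantity shown.

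**Working it through.** **Inputs.** The point rests on no figure stated in the protocol; the sample size only sets n. Section 4.4 gives 33 low-SMM patients per arm and 5% drop-out: 2 × 33 = 66, and 66 / 0.95 = 69.5, rounded up to 70. Section 8.2 allocates 1:1, so n = 35 per arm. For 55.7% versus 86.3%, two-sided alpha 0.05 and 80% power, the usual normal approximations give 34 (pooled) and 31 (unpooled), so the stated 33 is in line. Section 10 sets two-sided 0.05. The count distributions below are assumptions.

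**Step 1: equal medians, unequal means.** For a Poisson mean of 2.7, P(X ≤ 2) = 0.494 and P(X ≤ 3) = 0.714, so the median is 3. For 3.6, P(X ≤ 2) = 0.303 and P(X ≤ 3) = 0.515, so the median is again 3. The standard error of the difference in means is √((2.7 + 3.6)/35) = 0.424, and 0.9/0.424 = 2.12. With a critical value of 1.995 (68 df), the rejection probability is about Φ(2.12 − 1.995) ≈ 0.55. Simulation gives 55%.

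**Step 2: a range of assumed distributions.** Simulation with 35 per arm (20,000 runs; 4,000 for Mann-Whitney):

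| Assumed counts | Population medians | t-test significant | Mann-Whitney significant | t-test significant and observed medians identical |
|---|---|---|---|---|
| Poisson, means 2.0 vs 2.6 | 2 and 2 | 37% | 36% | 8% |
| Poisson, means 2.7 vs 3.6 | 3 and 3 | 55% | 53% | 6% |
| Poisson, means 1.7 vs 2.6 | 2 and 2 | 72% | 69% | 13% |
| Discrete, second arm right-skewed, means 2.0 vs 2.9 | 2 and 2 | 73% | 54% | 46% |

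The probabilities in the last row, for counts 0, 1, 2 and so on, are 0.10, 0.20, 0.40, 0.20, 0.10 in one arm and 0.05, 0.10, 0.40, 0.15, 0.12, 0.08, 0.05, 0.03, 0.02 in the other.

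**Step 3: the reverse case.** Take medians 2 and 3 with almost equal means. Counts 1 to 8 with probabilities 0.35, 0.40, 0.10, 0.05, 0.04, 0.03, 0.02, 0.01 have mean 2.25. Counts 0 to 5 with probabilities 0.20, 0.10, 0.15, 0.35, 0.15, 0.05 have mean 2.30. The t-test rejects in 6% of trials, close to its nominal level, although the medians differ.

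**Step 4: size under identical distributions.** With Poisson mean 2 in both arms the t-test rejects in 5.2% of trials. With negative binomial counts, mean 2 and dispersion k = 1 in both arms, it rejects in 4.5%.

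**Step 5: does the choice between t-test and Mann-Whitney matter?** For negative binomial counts with means 3.0 and 4.2 and the same k in both arms, rejection by t-test and Mann-Whitney is 72% vs 68% (k = 50), 50% vs 47% (k = 5), 34% vs 30% (k = 2) and 25% vs 21% (k = 1.2). A wide gap, 28% vs 7–8%, appears when one arm has k = 50 and the other k = 1.2. The variances are then 3 + 9/50 = 3.2 and 4.2 + 17.64/1.2 = 18.9, a ratio of about six.

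**The case against.** The best defence is that this is a wording slip with little consequence. Section 10 plans normality checks and has the Mann-Whitney test available. Section 10.2 also compares the proportion of patients with one or more toxicity events by Fisher's exact test, so the toxicity comparison does not rest on the t-test alone. The outcome is secondary. All of that stands as a limit on importance. It does not repair the sentence, because the general list attaches no test to this endpoint and the specific sentence names only the t-test.

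A reader might infer three stronger things that the document does not support.

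- That the t-test produces false positives here. It does not. Its size is about 5% when the distributions are identical (Step 4), and a significant result with equal medians reflects a real difference in means.
- That a few patients with many events would drive the result, so that t-test and Mann-Whitney would disagree widely. No count distribution is given, and counting each toxicity type once per period works against long tails. With similar dispersion in both arms the tests differ by a few percentage points. A wide gap needs arms that differ strongly in spread (Step 5).
- That replacing the t-test by Mann-Whitney would tie the p value to the median. Mann-Whitney is not a test of medians either: it rejected in 36% to 69% of the equal-median cases in Step 2.

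**Conclusion.** The sentence is wrong as written: the summary is a median and the test is a test of means. Under the assumed distributions with equal population medians and 35 per arm, the t-test was significant in 37% to 73% of trials. In 6% to 46% of all trials it was significant while the two observed medians were also identical. These percentages depend wholly on assumed counts. They show that the mismatch can matter; they do not predict this trial.

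The consequence is limited to how a secondary toxicity result is read. Type I error, the primary endpoint and the sample size are not affected. The t-test itself is not disqualified; it has to be paired with the quantity it tests.

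**What to change.** Reword the one sentence in section 10.2 so that summary and test agree, for acute and late counts alike. Either of these would do:

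- Report the mean number of toxicity events per patient by arm, with the difference in means and 95% CI from a Welch t-test, or a rate ratio with 95% CI from a negative binomial or robust Poisson model.
- Keep medians and IQR as description, and compare the arms with a rank-based test (Mann-Whitney, or van Elteren stratified by the randomisation strata). State that it tests a shift in distribution, not a difference in medians.

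The smallest change is to replace the median by the mean and keep a t-test. The count model is a reasonable choice but is not needed to remove the contradiction. The cost is one sentence, with no new data and no change to the sample size; it should be settled before the toxicity data are analysed.

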### Primary Objective:

- To compare the compliance rate to proposed cisplatin scheme between weekly low dose cisplatin or three-weekly high dose cisplatin in patients with low SMM.

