### Secondary Objective(s):

- To investigate whether weekly low dose cisplatin can increase the compliance to the planned chemotherapy scheme in LA-HNSCC patients with low SMM to a level of compliance to three-weekly high dose cisplatin of patients without low SMM.
- To investigate treatment cumulative cisplatin dose in patients with low SMM receiving weekly low dose or three-weekly high dose cisplatin.
- To investigate acute and late adverse events/toxicity in patients with low SMM receiving weekly low dose or three-weekly high dose cisplatin.
- To investigate time to recurrence in patients with low SMM receiving weekly low dose or three-weekly high dose cisplatin.
- To investigate 2-years survival in patients with low SMM receiving weekly low dose or three-weekly high dose cisplatin.
- To investigate quality of life in patients with low SMM receiving weekly low dose or three-weekly high dose cisplatin.
- To investigate costs in care for patients with low SMM receiving weekly low dose or three-weekly high dose cisplatin.
- To investigate patient's preference of treatment in patients with low SMM receiving weekly low dose or three-weekly high dose cisplatin.

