### 3. STUDY DESIGN

In this multicenter prospective randomised low intervention clinical trial, the compliance of weekly low dose cisplatin with concurrent radiotherapy in LA-HNSCC patients with low SMM will be investigated. SMM will be measured on routinely performed (PET-)CT or MRI scans before the multidisciplinary head and neck cancer meeting by the treating physician. Patients who are found eligible by the multidisciplinary team and are planned for cisplatin based concurrent CRT will be asked to participate in this study by the investigator. Seventy patients with low SMM will be randomised between weekly low dose and three-weekly high dose cisplatin. To assure the inclusion of seventy patients with low SMM, 129 patients in total are needed as explained in paragraph 4.4. Therefore 59 patients with normal skeletal muscle mass will be asked to participate as well. They will receive the most standard cisplatin scheme for the centre they are admitted to specifically and will be included in follow-up. Baseline characteristics and outcomes will be collected for all patients.

SMM will be estimated using a validated technique based on measurement of the cross-sectional area of the sternocleidomastoid muscle and paravertebral muscles on the level of C3 on routinely performed CT or MRI. In patients who underwent fluorodeoxyglucose-positron emission tomography(FDG-PET)/CT as part of the diagnostic work-up, as a control of SMM measurement at the level of C3, SMM will also be measured at the level of L3, which is the most commonly used method in medical literature as a control of SMM measurement at the level of C3.

Based on the cut-off value calculated by Wendrich et al., low SMM is defined as skeletal muscle mass  $\leq 43,3 \text{ cm}^2/\text{m}^2$ . Patients with low SMM will be randomised between weekly low dose cisplatin and three-weekly high dose cisplatin with concurrent RT. The rate of compliance to proposed cisplatin scheme will be compared between three groups: patients with low SMM with weekly low dose cisplatin, patients with low SMM and three-weekly high dose cisplatin and the rest group of normal SMM receiving the local standard scheme, which is three-weekly 100 mg/m^2 cisplatin in the UMC Utrecht, Noordwest Ziekenhuisgroep, Leiden University Medical Center, and VUmc, and weekly 40 mg/m^2 cisplatin in the NKI-AVL.

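### Section 10.2 tests survival and recurrence only across three groups, one of them the non-randomised normal-SMM cohort, although the matching objectives concern the two randomised low-SMM arms

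*Protocol*

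**What the plan says.** Section 10.2 states that overall survival, disease-specific survival, loco-regional recurrences and time to recurrence are "compared between the three groups by the log-rank test", in the intention-to-treat population. It adds hazard ratios from a univariate Cox model, and an assessment of randomised treatment in a multivariate Cox model. It does not say which patients enter either model.

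Section 3 defines the third group: "59 patients with normal skeletal muscle mass will be asked to participate as well", and "They will receive the most standard cisplatin scheme for the centre they are admitted to specifically". That scheme is three-weekly in four centres and weekly in one.

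The objectives in Section 2 are narrower. Two secondary objectives read "To investigate time to recurrence in patients with low SMM receiving weekly low dose or three-weekly high dose cisplatin" and "To investigate 2-years survival in patients with low SMM receiving weekly low dose or three-weekly high dose cisplatin". The primary objective is "To compare the compliance rate to proposed cisplatin scheme between weekly low dose cisplatin or three-weekly high dose cisplatin in patients with low SMM".

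On compliance, Section 3 says "The rate of compliance to proposed cisplatin scheme will be compared between three groups". Section 10.1 gives the primary parameter as "compliance (non CDLT) rate to the proposed cisplatin scheme in the intention-to-treat population" and names neither the groups nor the test.

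**The concern.** A three-group log-rank test has two degrees of freedom and asks whether any group differs from the others. The objectives ask a one-degree-of-freedom question about two randomised arms.

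The third group differs from the other two by its muscle mass, which is the characteristic the trial is built on. It also mixes both schedules according to centre. A small p value could therefore come from muscle mass, or from centre and local schedule, and still be reported against an objective about the randomised schedules. Conversely, a real schedule effect is spread over an extra degree of freedom.

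The test is also placed in an intention-to-treat population, a term with no clear meaning for patients who were never randomised.

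Section 8.1.2 calls time to recurrence and survival the main oncological outcomes, so this is the analysis that readers would turn to after compliance.

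**Working it through.** **1. What the trial was sized for (Section 4.4).** Inputs: compliance 55.7% and 86.3%, two-sided alpha 0.05, power 80%. Mean rate = (0.557 + 0.863)/2 = 0.71; difference = 0.306.

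n per arm = [1.96·√(2·0.71·0.29) + 0.8416·√(0.557·0.443 + 0.863·0.137)]² / 0.306² = (1.2577 + 0.5085)² / 0.0936 = 33.3, so 34.

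The protocol states 33, within one patient. Then 66/0.95 = 69.5, so 70; 70/0.545 = 128.4, so 129; 129 − 70 = 59. The plan's figures hold and are for a **two-arm** comparison. The 59 are a by-product of finding 70 low-SMM patients.

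**2. A low/normal-SMM hazard ratio from protocol figures.** The protocol gives no survival by SMM. Section 1 gives 3-year survival of 72% and 52% by completion of cisplatin. Assume exponential survival, and assume SMM acts on survival only through compliance.

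- 2-year survival: 0.72^(2/3) = 80.3% with completion and 0.52^(2/3) = 64.7% without.
- Low SMM: 0.557·80.3 + 0.443·64.7 = 73.4%.
- Normal SMM: 0.863·80.3 + 0.137·64.7 = 78.2%.
- Hazard ratio = ln(0.734)/ln(0.782) = 1.26.

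The simulation used 1.27. Values of 1.5 and 2.0 are assumptions that show the range. The 72% and 52% imply ln(0.52)/ln(0.72) = 1.99, but that contrast is by completion of cisplatin, not by SMM.

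**3. Rejection rate with no schedule effect.** Simulation with 35/35/59 patients, exponential survival, normal-SMM 2-year survival assumed 78%, 26 months of observation, and identical hazards in the two randomised arms:

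| Low/normal-SMM hazard ratio | Three-group log-rank, p<0.05 | Two-arm log-rank, p<0.05 |
|---|---|---|
| 1.27 (protocol figures) | about 10% | about 5% |
| 1.5 (assumed) | about 19% | about 5% |
| 2.0 (assumed) | about 50% | about 5% |

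A second set of runs, with 24 months of observation and low-SMM 2-year survival assumed at 60% to 70%, gave 18–22% at 1.5 and 39–50% at 2.0. The two-arm test again stayed near 5%.

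**4. Power when the schedule does matter.** If weekly dosing halved the hazard (low/normal hazard ratio 1.5 assumed for the three-weekly arm), power is about 23–25% for the three-group test and 30% for the two-arm test.

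**5. Compliance, conditionally.** Suppose Section 3 were carried out as a 2×3 chi-square test, with 55.7% in both randomised arms and 86.3% in the cohort. It would be significant in about 95% of trials, against about 4.5% for the two-arm test. No section specifies that 2×3 test.

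**The case against.** **The Cox models already address the randomised contrast.** This stands in part. Section 10.2 does plan hazard ratios with confidence intervals and an adjusted analysis of randomised treatment. But the adjusted analysis is described as an addition, and neither model is limited to the 70 randomised patients. The only log-rank comparison named remains the three-group one. Elsewhere in the same section, toxicity and cumulative dose are compared between trial arms, so the switch to three groups is specific to the time-to-event outcomes.

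**The primary compliance analysis is not affected.** This stands. The Summary, Section 2 and Section 4.4 all set the primary comparison as weekly versus three-weekly in low-SMM patients. A reader might infer from Section 3 that the primary test is an omnibus three-group test with a 95% chance of a spurious result. The documents do not support that: Section 3 names no test, and its sentence can be read as serving the first secondary objective, which needs the normal-SMM compliance rate. What remains is an inconsistency of wording.

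**Rejection should not be expected for survival.** This also stands. A reader might infer that the three-group log-rank will be significant merely because normal-SMM patients are presumed to do better. The one hazard ratio built from protocol figures gives about 10%, and the larger rates rest on assumed ratios.

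**The cohort cannot be left out of all inference.** This stands too. The first secondary objective asks whether weekly compliance in low SMM reaches that of normal-SMM patients on the three-weekly scheme. That needs its own comparison, which an omnibus test would not supply.

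**Conclusion.** The concern holds for the time-to-event endpoints. Section 10.2 names a test that does not match the survival and recurrence objectives and includes a non-randomised group. For the randomised question, it roughly doubles the nominal 5% error at the hazard ratio built from protocol figures (about 10%). At assumed ratios of 1.5 and 2.0 the error reaches about 19% and 50%. The loss of power is modest, about 23–25% against 30% in the case examined, and neither test is well powered.

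These figures rest on exponential survival, an assumed 2-year survival, and low/normal-SMM hazard ratios that the protocol does not report. The mismatch between test and objective does not depend on them.

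For compliance, the point is limited to aligning Section 3 with the rest of the protocol. Overall this is a wording correction for secondary endpoints, not a must-fix for the primary analysis.

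**What to change.** - **Section 10.2:** make the log-rank test and both Cox models a comparison of the two randomised low-SMM arms. State that the intention-to-treat population is the randomised low-SMM patients. Show the normal-SMM cohort's survival and recurrence separately, for example as Kaplan-Meier curves with 95% confidence intervals, labelled as a non-randomised reference.
- **Section 3 (and 10.1 for clarity):** say that the primary compliance test compares the two randomised arms, in line with Sections 2 and 4.4.
- **First secondary objective:** describe the comparison of low-SMM weekly with normal-SMM three-weekly compliance as a separate, non-randomised pairwise comparison, reported as a difference with a confidence interval. Normal-SMM patients treated weekly under their centre's standard do not belong in that comparator.

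The cost is a few sentences. No patients or data are added, and the only thing lost is the omnibus three-group p value, which answers none of the stated objectives.
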